### Plans to promote participant retention and complete follow-up {18b}

The full compensation for study participation and inconveniences (e.g., travel costs) will be paid at the last assessment point (follow-up) to increase motivation to complete all treatment visits. All participants will be equipped with an appointments card and be encouraged to save appointments in their calendars at the beginning of the study in order to promote retention at all assessment points. We also combine several study visits where possible (e.g., pre-treatment measurements and first treatment), in order to reduce the number of study visits to a manageable number, whilst keeping treatment visits close to usual treatment schedules (i.e., one visit per week). Participants who wish to discontinue the study will be asked to fill in a form to assess reasons for discontinuation (e.g., time commitment, adverse effects, other) and will also receive partial compensation. This data will be used to assess whether missing data is likely to be in relation to the interventions themselves.

### Data management {19}

All survey data is entered digitally by the participant via the web-based Lime Survey platform (Lime Survey, Hamburg, Germany) at our study facility. All participant data is anonymized with encryption-based pseudonymization using a software solution (ALIIAS) developed by the TRR/CRC 289, which integrates with the Lime Survey platform and allows for a two-factor authentication via hardware security tokens [71]. The pseudonymization procedure is in accordance with the Declaration of Helsinki, European Directives 2001/20/EC, 95/46/EC, Regulation (CE) No 45/2001 and the General Data Protection Regulation (GDPR, 2016/679) of the EU. The anonymized data is stored centrally on the server of the University Duisburg-Essen. Because the self-report measures are collected in the Lime Survey platform, only valid values can be entered. Nonetheless, range checks of all instruments will be performed as part of the analysis process.

The expert ratings collected during the diagnostic interviews are recorded on paper and entered into a password secured digital document after the appointment. After each diagnostic interview, research staff double check if MADRS scores were calculated correctly by the clinician in the paper version and transferred correctly into the digital document. Again, range checks will be performed before the analysis.

### Confidentiality {27}

Each participant receives a randomization number and a pseudonymized code upon randomization. The randomization number is used to refer to the participant during the trial in our internal procedures. No personal information stored against this number. The pseudonymized code is generated using the ALIIAS anonymization system and all survey data is stored against this code in the Lime Survey cloud [71]. The code can only be traced back to the personal information with a hardware key, which is kept in a locked location that only study staff have access to (for a detailed description of the ALIIAS pseudonymization process, see [71]).

Emails and email addresses of potential participants are kept in our study email account (university email account) and only the research staff in this study, who have signed a confidentiality agreement have access to this account. Handwritten documentation about each participant’s study visits (appointment check lists, diagnostics and other written material) is kept in folders that are locked in a file-drawer in the locked study room, which only the research staff of this study have access to. The data is kept for a maximum of 10 years and is continually kept in a locked location at the study center at the University of Marburg. Personal information (i.e., name, email address, phone number) used to contact participants is kept separately from the written documentation and the pseudonymised data contained in the ALIIAS system and is destroyed after trial. Any documentation that is saved digitally in our local server, for example to track the progress of the trial, does not contain personal information and is password-secured. Participants who wish to be referred to and contacted by the outpatient clinic after the trial give their consent to pass on their contact details to the outpatient clinic.

### Plans for collection, laboratory evaluation, and storage of biological specimens for genetic or molecular analysis in this trial/future use {33}

Cortisol and alpha amylase samples will be collected at our outpatient clinic and sent to the laboratory at the University of Essen for analysis.

## Statistical methods

### Statistical methods for primary and secondary outcomes {20a}

Multivariate procedures with repeated measures will be used to test the main hypothesis (*F*-statistics). The main analysis of interest is the difference in mean change in the primary outcome (MADRS score) from baseline to post-intervention measurement. In addition, linear mixed-effect models with baseline adjustment will be calculated, based on the generalized covariance matrix. Main effects for group, time, and the group-time interaction will be analyzed. The main analyses are based on intention-to-treat (ITT) models. The predefined covariate variables such as subjective pre-existing attitudes of the participants will be included as covariates. Secondary outcomes of interest, namely subjective depressive symptoms, disability, state anxiety, and perceived stress, will be analyzed with the same strategy as described above.

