### Outcomes {12}

Since this trial focusses on major depression, the primary outcome will be depression severity assessed at baseline and post-treatment with the expert rating version of the Montgomery Asberg Depression Scale (MADRS) [50]. Subjective depressive symptoms are assessed with the German version of the Beck Depression Inventory (BDI-II) [51] at baseline, post-intervention, and at follow-up, as a secondary outcome. Using these widely used assessment scales is clinically relevant, as expert ratings and subjective assessments of depressive symptoms can vary significantly. By employing both scales, a more comprehensive understanding of changes in symptomatology can be obtained.

Other clinically relevant self-report outcome measures include the German version of the Pain Disability Inventory (PDI) [52] to measure stress and illness burden; the perceived stress scale (PSS-10) [53], both assessed before the allocation, post-treatment, and at follow-up; and the state-subscale of the State-Trait-Anxiety-Depression-Inventory (STADI) [54], which is assessed at baseline, before the allocation, post-treatment, and at follow-up. Changes in treatment expectations prior to the intervention are measured with the following self-report instruments: Treatment Expectation Questionnaire (TEX-Q) [55] and the Generic rating scale for previous treatment experiences, treatment expectations, and treatment effects (GEEE) [56], both assessed at baseline and after the allocation. Side effects and potential harm is measured before the allocation, post-treatment, and at follow-up with the generic assessment of side-effects scale (GASE) [57] (for a detailed description of all variables, see the “Plans for assessment and collection of outcomes {18a}” section).

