## Data collection and management

### Plans for assessment and collection of outcomes {18a}

#### Primary outcome

The primary outcome is the change in depression severity as measured by the expert rating version of the Montgomery Asberg Depression Scale (MADRS) [50]. The MADRS assesses the following: apparent sadness, reported sadness, inner tension, reduced sleep, reduced appetite, concentration difficulties, lassitude, inability to feel, pessimistic thoughts, and suicidal thoughts. Each item is scored on a scale from 0 (no/hardly any difficulties) to 6 (extreme difficulties). Total scores between 7 and 19 indicate a mild depression, scores between 20 and 34 moderate depression, and a score above 34 severe depression [60]. This scale was shown to achieve high reliability of total and item scores in depressed populations [61]. Blinded and trained clinicians undertake the MADRS assessment at baseline and post-intervention. The outcome assessors are trained to rate the MADRS scores alongside the depression section in the Structured Interview for DSM-5 (SCID-5) diagnoses. A random selection of videotaped MADRS ratings will be rated a second time by independent raters to establish inter-rater reliability.

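### The main MADRS test is a change score not adjusted for baseline MADRS, and the additional baseline-adjusted mixed model with time effects is ill-specified for an outcome rated only twice

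*Protocol article*

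**What the plan says.** The primary outcome section fixes two ratings: "Blinded and trained clinicians undertake the MADRS assessment at baseline and post-intervention". The follow-up visit has no MADRS.

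The section on statistical methods for primary and secondary outcomes {20a} then sets out:

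- the test family: "Multivariate procedures with repeated measures will be used to test the main hypothesis";
- the estimand of that test: "The main analysis of interest is the difference in mean change in the primary outcome (MADRS score) from baseline to post-intervention measurement";
- a further model: "In addition, linear mixed-effect models with baseline adjustment will be calculated, based on the generalized covariance matrix";
- its effects: "Main effects for group, time, and the group-time interaction will be analyzed";
- covariates: "The predefined covariate variables such as subjective pre-existing attitudes of the participants will be included as covariates".

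The section on pre-defined covariates lists trait STADI, SSAS, BIS/BAS, prior treatment experience and salivary stress markers. Baseline MADRS is not on the list. The secondary outcomes "will be analyzed with the same strategy as described above".

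**The concern.** There are two separate issues.

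1. **Efficiency of the main test.** With two ratings per patient, the group-by-time F-test in a repeated-measures analysis is the test of the difference in mean change. It subtracts the whole baseline value, whatever the correlation. ANCOVA subtracts only as much as the data support. Baseline MADRS is collected on everyone, so leaving it out of the model costs precision for no gain.

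2. **Meaning of the additional model.** Baseline adjustment and a time effect do not fit together for MADRS. If baseline moves to the right-hand side, one outcome value per patient remains and time is not a factor. If baseline stays as an outcome row and is also a covariate, the covariate cancels from the interaction.

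At stake are power for the congruent versus incongruent comparison, and a supporting analysis that cannot be fitted as described or only repeats the main one.

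**Working it through.** **Inputs from the article.** Two MADRS ratings (Outcomes; Primary outcome). d > 0.40, power 0.90, alpha 0.05, a minimum of 96 patients in the 2 × 2 part, 20% drop-out, four groups of 30 (Sample size). The main contrast is congruent versus incongruent (Natural course group), which gives 48 versus 48 at N = 96.

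**Assumptions.** The article gives neither r, the correlation between baseline and post-treatment MADRS, nor the SD to which d refers. I take r from 0.3 to 0.8, equal SD (set to 1) at both visits, d = 0.40 on that raw SD, and a two-sided 5% level.

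**The article's own figure.** For a group-by-time F-test with 4 groups and 2 measurements, λ = f²·N·m/(1−r). With f = d/2 = 0.20 and r = 0.5, λ at N = 96 is 0.04·96·2/0.5 = 15.36 on 3 and 92 df, and power is 0.912 (0.898 at N = 92). So 96 is reproduced, and 96/0.80 = 120 = 4 × 30. Other routes also give 96, so the route used cannot be told.

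**Variances.**

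- Change score: 1 + 1 − 2r = 2(1−r).
- ANCOVA residual: 1 − r².
- Ratio: (1−r)(1+r) / [2(1−r)] = (1+r)/2.

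**Power and size.** Power = Φ(0.40/√(2V/48) − 1.96), with V the variance above. Example at r = 0.5: change V = 1.00, SE = √(2/48) = 0.204, power 0.50; ANCOVA V = 0.75, SE = √(1.5/48) = 0.177, power 0.62.

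| r | ratio | power, change | power, ANCOVA | total N for 90%, change | total N for 90%, ANCOVA |
|---|---|---|---|---|---|
| 0.3 | 0.65 | 0.38 | 0.54 | 368 | 240 |
| 0.5 | 0.75 | 0.50 | 0.62 | 264 | 198 |
| 0.7 | 0.85 | 0.72 | 0.78 | 158 | 134 |
| 0.8 | 0.90 | 0.87 | 0.90 | 106 | 96 |

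If d = 0.40 is instead meant on the SD of change, change-score power is 0.50 at every r, and ANCOVA power is 0.68, 0.62, 0.57 and 0.54 at r = 0.3, 0.5, 0.7 and 0.8.

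**Validity of the main test.** In 2,000 simulated null trials per value (48 versus 48; r = 0.3, 0.5, 0.7), type I error was 0.058, 0.054 and 0.051 for the change score and 0.050, 0.056 and 0.056 for ANCOVA. Both estimated the effect without bias.

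**The additional model, reading by reading.**

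- *Baseline only as covariate.* One row per patient remains. There is no time effect and no group-time effect. The model is then the ANCOVA.
- *Baseline as covariate and as outcome row.* The covariate has the same value in both rows, so it cancels from post minus baseline, and the interaction estimate is the raw difference in mean change. The rest depends on the covariance structure:
  - Compound symmetry: type I error 0.058, 0.054 and 0.050, power 0.37, 0.49 and 0.72, in effect the change-score test.
  - Unstructured: the baseline row is predicted exactly by its own covariate (coefficient 1, residual variance about 0), and the covariance was singular in 500 of 500 runs at r = 0.5.
  - Random intercept: the residual covariance within patient is −(1−r)²/4, which a non-negative intercept variance cannot represent. With that variance at zero, the standard error is too small, and type I error was 8.2%, 7.0% and 6.3% at r = 0.3, 0.5 and 0.7.
  - The group main effect averages both rows and is halved (−0.19 when the interaction is −0.39).
- *Baseline in the response with a common mean across arms.* This works. Its power was 0.53, 0.61 and 0.78, matching ANCOVA. It has no group main effect, which does not fit the effects that the article lists.

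**The case against.** The best defence is that nothing here is invalid. In a randomised trial the change-score test is unbiased and holds its level. The article is condensed, and the form of the mixed model can be left to an analysis plan that is not shown. The mixed model also has a proper use: BDI-II, PDI, PSS-10 and state STADI have a follow-up value, so time and group-time effects mean something there. The power gain rests on an r that the article does not give, and it shrinks to a few points at r = 0.8.

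Much of this stands. What remains is what the article does fix: a change score as the main MADRS analysis, a covariate list without baseline MADRS, and a pair of model features that do not go together for a twice-rated outcome.

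Three stronger readings are tempting, and the article does not support them.

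- *The primary analysis is left undecided.* The article ranks the two: mean change is named as the main analysis, and the mixed model is introduced as an addition.
- *Success on either analysis inflates type I error.* Given that ranking, no either-of-two rule is planned.
- *The mixed model is anti-conservative.* The 6% to 8% error needs a random intercept at its zero boundary. The article names no random intercept, its reference to a generalized covariance matrix leaves the structure open, and compound symmetry gives about 5%.

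It would also be too broad to call the main test wholly unadjusted, since the predefined covariates are to be included. What is missing is baseline MADRS.

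**Conclusion.** The point holds as one of efficiency and clear specification, not of validity. The main MADRS test has a variance 2/(1+r) times that of ANCOVA: 1/0.65 = 1.54 times at r = 0.3 and 1/0.90 = 1.11 times at r = 0.8. With d = 0.40 on the raw SD and 48 versus 48, this costs about 16 percentage points of power at r = 0.3, 12 at 0.5, 7 at 0.7 and 3 at 0.8. These figures depend on the assumed r and on the scale of d. Whether 96 patients are enough is a matter for the sample size section and is not decided here.

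The additional model cannot be fitted to MADRS as described without dropping either the time effects or the meaning of the adjustment. If baseline is kept on both sides, the fit may be redundant, singular or too optimistic in its standard error, depending on a covariance structure that the article does not specify.

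**What to change.** In the statistical methods section:

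1. Make one analysis primary for MADRS: ANCOVA of post-treatment MADRS on baseline MADRS, rationale, treatment and rationale × treatment. The last term carries the congruent versus incongruent contrast. A longitudinal model with baseline in the response and baseline means constrained equal across arms is an equivalent choice.
2. Label the repeated-measures F-test of mean change supportive.
3. Drop the baseline-adjusted model with time and group-time effects for MADRS.
4. For secondary outcomes with a follow-up, use baseline as a covariate and only the post-treatment and follow-up values as outcomes.

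The cost is wording in the analysis plan, with a matching amendment. Baseline MADRS is already collected, and no visit, assessment or patient is added.

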### Trial design {8}

In this participant and rater-blinded randomized controlled trial (RCT), four parallel experimental treatment arms are compared to each other. Equal sample sizes are allocated to all groups (*N* = 30). Superiority of the four experimental conditions over the natural course group (5th group) is assumed as well as superiority of the two congruent treatment arms over the incongruent treatment arms.

This protocol is reported according to the standard protocol items: recommendation for interventional trials (SPIRIT) guidelines. The SPIRIT figure detailing the schedule of enrollment, interventions, and assessments is provided in Fig. 1.

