## Interventions

### Explanation for the choice of comparators {6b}

One aim of this study is to assess the size of the placebo effect in the treatment of depression more generally. Since major depression is routinely treated with pharmacological agents (antidepressants) and/or with psychotherapy, two active placebo treatments are compared to each other: an active pharmacological placebo and an active psychological placebo.

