#### Natural course group

Few clinical studies in the field of antidepressant placebo research include a natural course control group and thus are not able to differentiate between placebo effects and spontaneous remission in the course of the disorder [10]. To control for potential regression to the mean and spontaneous improvement in the outcome variables, we employ a natural course group.

The main aim of this study is to assess how a placebo response in the treatment of depression can be modified by manipulating the patient-clinician communication during the communicated illness and treatment rationale. Thus, the main comparators are the intervention groups who receive congruent vs. incongruent illness and treatment rationales.

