### Sample size {14}

We expect a difference of effects on the primary outcome between treatments with congruent versus incongruent contents of a priori provided treatment rationales. Based on previous research [58], we expect an effect size of Cohen’s *d* > 0.40. Our primary hypothesis comprises of the comparison of the clinical status before and after treatment using the MADRS as the primary outcome. A power of 0.90 and alpha < 0.05 and a 2 × 2 design (treatment rationale, active placebo) requires a minimum of 96 participants. Considering a 20% drop-out/treatment discontinuation, 4 groups of 30 participants are required. The 5th group (natural course) does not serve hypothesis testing. Therefore, this group is not considered in the power calculation. Based on the 5 arms in the study, a total of 150 participants are required.

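### The primary analysis names only an undefined 'group' factor and no congruency contrast, so what the deciding F-test would show is left open, and the natural course arm's role is stated inconsistently

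*Protocol article*

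**What the plan says.** **The comparison of interest.** The first hypothesis is that a rationale matching the treatment gives a better outcome than one that does not. The section on the natural course group states that "the main comparators are the intervention groups who receive congruent vs. incongruent illness and treatment rationales". Sample size {14} agrees: "We expect a difference of effects on the primary outcome between treatments with congruent versus incongruent contents of a priori provided treatment rationales". It then sizes the trial for a 2 × 2 design with the factors treatment rationale and active placebo.

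**The analysis.** Statistical methods {20a} opens with "Multivariate procedures with repeated measures will be used to test the main hypothesis", by F-statistics, and continues: "The main analysis of interest is the difference in mean change in the primary outcome (MADRS score) from baseline to post-intervention measurement". It does not say between which groups. Mixed models with baseline adjustment are added, followed by "Main effects for group, time, and the group-time interaction will be analyzed". Neither a rationale factor, a treatment factor, their interaction nor a congruency contrast appears. Secondary outcomes follow the same strategy.

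**The natural course arm.** Trial design {8}: "Superiority of the four experimental conditions over the natural course group (5th group) is assumed". The section on comparators {6b} sets a related goal: "One aim of this study is to assess the size of the placebo effect in the treatment of depression more generally". Sample size {14}: "The 5th group (natural course) does not serve hypothesis testing". The statistical section does not say whether this arm enters the model.

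**The concern.** In the 2 × 2, congruency is one specific comparison with one degree of freedom: the rationale-by-treatment interaction on MADRS change. The statistical section uses different terms from the sample size section, and one undefined word decides which hypothesis the F-test addresses.

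The protocol supports several meanings of *group*:
- **Two levels:** congruent versus incongruent (Natural course group; Sample size {14}).
- **Three levels:** congruent, incongruent, natural course (Participant timeline {13}).
- **Four levels:** the intervention arms (Intervention description {11a}; Sample size {14}).
- **Five levels:** all randomized arms (Sequence generation {16a}; the methods for missing data {20c} analyse everyone randomized).

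Under the last three, a significant result may reflect only that pill and writing differ, or that placebo differs from no treatment. Both are plausible on the protocol's own account: Trial design {8} expects all four arms to beat natural course, and the limitations section warns that the clinic setting may favour the psychological arm. If the meaning is not fixed beforehand, it can be chosen after the data are seen.

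**Working it through.** **Inputs.** From Sample size {14}: d = 0.40, power 0.90, alpha 0.05, 96 analysable participants (24 per arm), 30 per arm randomized. Assumed, because the article gives no such figures: a common SD for the analysed MADRS outcome, in whose units the differences below are expressed; non-congruency differences δ of 0.3, 0.5 and 0.8 SD; and a pre-post correlation r where needed. All power values come from the noncentral F distribution at alpha 0.05.

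**1. The plan's own figure.** For a repeated-measures group-by-time test with four groups and m = 2 time points, take f = d/2 = 0.20 and λ = f² × N × m / (1 − r).
- r = 0.5, N = 96: λ = 0.04 × 96 × 2 / 0.5 = 15.36. With 3 and 92 df, power is 0.912. At N = 92 it is 0.898. The smallest N is 93, which becomes 96 with equal arms, and 96 / 0.80 = 120 = 4 × 30.
- r = 0.3, N = 96: λ = 0.04 × 96 × 2 / 0.7 = 10.97. With 1 and 92 df, power is 0.906. The smallest N is 94, again 96 with equal arms.

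So 96 is consistent with a 3-df four-arm test and also with a 1-df test. It does not settle which was planned.

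**2. Chance of a significant F with no congruency effect.** λ = Σ nᵢ(μᵢ − μ̄)².
- *Four arms, pill and writing differ by δ:* λ = n × 4 × (δ/2)² = nδ². For n = 24 and δ = 0.5, λ = 6.0 on 3 and 92 df.
- *Five arms, natural course differs from four equal arms by δ:* λ = n × [4(δ/5)² + (4δ/5)²] = 0.8nδ² = 4.8 on 4 and 115 df.
- *Three levels (48, 48, 24), same difference:* λ = 4.8 on 2 and 117 df.

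| Reading of *group* | δ = 0.3 | δ = 0.5 | δ = 0.8 | δ = 0.5, n = 30 |
|---|---|---|---|---|
| Four arms (3 df) | 0.198 | 0.499 | 0.912 | 0.607 |
| Five arms (4 df) | 0.148 | 0.366 | 0.795 | 0.456 |
| Three levels (2 df) | 0.196 | 0.476 | 0.882 | 0.575 |

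In simulation (20,000 runs, δ = 0.5), the single congruency contrast in the four intervention arms rejected in 4.9% of trials, both when pill and writing differed and when natural course differed. If *group* has only the two congruency levels, group-by-time is that contrast and there is no excess.

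**3. Power for a true congruency effect.** With congruent and incongruent arms 0.40 SD apart, λ = 24 × 0.40² = 3.84. On 3 df the power is 0.33, and on 1 df it is 0.49 (0.41 and 0.58 at 30 per arm). These are lower than the 0.912 in step 1 because that formula multiplies λ by m/(1 − r) = 4 (15.36 against 3.84). On that scale the corresponding powers are 0.91 (3 df) and 0.97 (1 df). The single contrast has the higher power on either scale.

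**4. The natural course statements.** Trial design {8} states superiority over this arm and the comparator section makes the size of the placebo effect an aim. Sample size {14} excludes the arm from hypothesis testing. With 24 in this arm and 96 pooled, the 95% CI half-width is 1.96 × √(1/24 + 1/96) = 0.45 SD. For a single arm against it, the half-width is 1.96 × √(2/24) = 0.57 SD. The pooled comparison can be reported as an estimate without any test.

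**The case against.** A reader might infer that the plan tests an omnibus group effect in place of the congruency hypothesis. The text does not show that. *Group* is undefined, and the natural course and sample size sections permit a two-level reading under which group-by-time is exactly the right test. The sentence listing the terms follows the additional mixed models and may describe only those. Listing main effects beside an interaction is ordinary model description and does not make each a confirmatory test.

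The five-arm reading is at odds with the statement that the fifth arm serves no hypothesis test. The superiority wording may express an expectation, and assessing the size of a placebo effect is estimation. The 0.5 SD differences are illustrative. Finally, this is a condensed article, and factor coding is often left to the analysis plan.

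Most of this stands, and it makes the rejection rates conditional on the reading. It does not remove the point. The section does fix model terms, gives no others for the main F-test, and those terms do not match the two factors on which the trial was sized. The statements about the natural course arm also need reconciling within this document, whatever a separate plan says.

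**Conclusion.** The point holds as a should-fix: the primary test is not tied to the congruency hypothesis, and the natural course arm's role is inconsistent. It is not established that the wrong hypothesis will be tested.

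The consequence depends on the meaning given to *group*. With two congruency levels, the false-positive rate for congruency stays at 5%. With three, four or five levels, the F-test is significant in about 37–50% of trials without any congruency effect, given 24 per arm and a 0.5 SD difference of another kind (15–20% at 0.3 SD, 80–91% at 0.8 SD). Under the four-arm reading, power for a 0.40 SD congruency effect falls from 0.49 to 0.33. These figures rest on a common SD and equal arms. That 96 can be reproduced with a 3-df test is suggestive only, since a 1-df test with a different assumed correlation gives it too.

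**What to change.** In Statistical methods {20a}, state that the sole primary test is the 1-df congruency contrast, (biological/pharmacological + psychological/psychological) minus (psychological/pharmacological + biological/psychological), on baseline-adjusted MADRS change from baseline to t6, in the four intervention arms only. In the repeated-measures model this is the rationale × treatment × time term. Report the two within-treatment simple effects (biological versus psychological rationale under pill, and under writing) as supporting estimates. Present other group and time effects as descriptive. Apply the same contrast to the secondary outcomes.

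The contrast takes the second incongruent arm to be biological/psychological, the remaining cell of the 2 × 2. The list in Intervention description {11a} labels it biological/pharmacological, which repeats the first arm, so that label should be reconciled too.

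Reword the superiority sentence in Trial design {8} so that the natural course comparison is a secondary or descriptive estimate, pooled placebo arms minus natural course with a 95% CI, outside the primary model. That agrees with Sample size {14} and still serves the aim of gauging the placebo effect.

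The cost is protocol and analysis-plan wording, with no new data or participants. It should be settled before any outcome data are examined by arm.
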